After each session, ORPHYS therapists will document all therapy sessions on a structured, standardized form, which includes the following information:◦ Date, time of the session, and setting◦ Suicidal thoughts and/or intentions based on a standardized operating procedure [90]◦ Short summary of the session◦ Thoughts on transference-countertransference based on the OPD-3 [89]◦ Psychological or psychiatric symptoms (e.g., mood, concentration, level of energy, level of activity), structural deficits based on the OPD-3 [91]◦ Medical treatment◦ Occurrence and severity of adverse events (AE, new psychological or physical symptoms, progress of disease, hospital admission, death, suicidal thoughts or attempts, difficulties in relationships or other areas of life) rated on a scale from 1 (mild) to 3 (severe), likelihood of an AE being related to the therapy rated on a scale from 1 (none) to 5 (definitely) [92]◦ Dropout (treatment, study, treatment-and-study dropout, or dropout due to adverse event)

Further, ORPHYS therapists will complete the WAI-SR [84].

Trained observers rate audio recordings and transcripts of therapy sessions to assess insight into repetitive dysfunctional relationship patterns and defense mechanisms. Insight is rated on a 5-point Likert-scale from 0 (not at all) to 4 (very much) using the 12-item Insight into Conflictual Relationship Patterns Scale (ICR, [93]). The total score ranges from 0 to 48. Higher scores indicate a more complex understanding of internal states and interpersonal processes. Defense mechanisms are rated by ranking the 150 items of the Q-sort version of the Defense Mechanisms Rating Scale (DMRS-Q, [94]) on an ordinal scale from 1 to 7. Qualitative and quantitative scores will be calculated using the DMRS-Q web-app (https://webapp.dmrs-q.com/).

Dosage and content of TAU treatment will be documented by the study personnel on a standardized form, which includes the following information.◦ Date, time of the session, and setting◦ Short summary of the session◦ Occurrence and severity of adverse events◦ Dropout

A semi-standardized section of the diagnostic interview will assess treatment dosage and frequency as well as utilization of further psychosocial support services (e.g., relaxation training, self-management programs).

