### Harms {17}

After each ORPHYS and TAU session, occurrence and severity of adverse events (new psychological or physical symptoms, progress of disease, hospital admission, death, suicidal thoughts or attempts, difficulties in relationships or other areas of life); serious adverse events (death, life-threatening event, prolonged or persistent disability or incapacity); and unanticipated events as well as their likelihood of being related to the treatment will be documented on a structured, standardized form [62, 92]. All adverse, serious adverse, and unanticipated events will be reported in trial publications.

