### Composition of the data monitoring committee, its role and reporting structure {28a}

A data-monitoring board, consisting of independent researchers with clinical and statistical expertise as well as expertise in the conduct of related clinical trials, will enable detection of potential adverse events (AE) early on and take appropriate measures due to close monitoring (documentation of therapy sessions, process variables) and supervision, thus minimizing the risk of serious AEs (SAE, suicidality, suicide). If the AE is treatment-related, it is characterized and documented as an adverse treatment reaction (ATR). Serious ATRs (death, life-threatening conditions, need for hospitalization) are reported immediately to the ethics committee. In case of suicidality, therapists are trained to follow a detailed standard operating procedure "suicidality" [88]. They will further contact the principal investigator and responsible local study manager immediately. Study personnel will discuss mild to moderate AEs (e.g., distress during the interviews) with patients and together they will decide on appropriate measures. If participants discontinue the trial or intervention, we document their reasons (e.g., study or treatment dropout due to an ATR) and assess consent or withdrawal from further assessments.

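### The Harms and data-monitoring sections give seriousness criteria that do not agree, so suicidality, treatment-related admission and disability are serious under one list and not under another

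*Protocol article*

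**What the plan says.** Harms {17} has two lists. The general adverse-event list includes "progress of disease, hospital admission, death, suicidal thoughts or attempts, difficulties in relationships or other areas of life". The serious list reads "serious adverse events (death, life-threatening event, prolonged or persistent disability or incapacity". The section adds that relatedness to treatment is documented after sessions in both arms, and that adverse, serious adverse and unanticipated events will all be published.

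The data monitoring section {28a} uses the term serious in two further ways. In describing what the monitoring board is for, it says "thus minimizing the risk of serious AEs (SAE, suicidality, suicide". It then defines a treatment reaction, "If the AE is treatment-related, it is characterized and documented as an adverse treatment reaction (ATR", and gives the reporting rule: "Serious ATRs (death, life-threatening conditions, need for hospitalization) are reported immediately to the ethics committee". For suicidality there is a standard operating procedure and an internal notification of therapists' superiors: "They will further contact the principal investigator and responsible local study manager immediately".

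Under Therapy process outcomes, the ORPHYS session form grades adverse events by severity, "rated on a scale from 1 (mild) to 3 (severe", and rates relatedness from 1 to 5. No criterion for seriousness is given there. For the control arm, "Dosage and content of TAU treatment will be documented by the study personnel on a standardized form"; the items listed for that form include occurrence and severity of adverse events but do not mention relatedness.

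**The concern.** Relatedness and seriousness are separate attributes. On the protocol's own definition, an adverse treatment reaction is an adverse event judged to be treatment-related, so relatedness should change the name of the event and leave its seriousness as it was. Here the criteria change with the section and with the name.

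Two things are at stake. The first is the published harms: serious and other adverse events are separate reporting categories, and the count in each depends on the list a site or analyst applies. The second is the immediate ethics-committee report, which is tied to the serious-reaction list and so does not cover everything that another list calls serious. The events concerned matter in this trial: suicidality is the risk the monitoring section singles out, death wishes are among the qualifying concerns for entry, and the Discussion expects hospital admissions to interrupt treatment.

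**Working it through.** There is no figure to reproduce and no arithmetic applies. The check sets the lists side by side.

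| Criterion | Harms {17}, serious list | {28a}, serious AEs named in the purpose statement | {28a}, serious treatment reactions |
|---|---|---|---|
| Death | yes | suicide only | yes |
| Life-threatening event or condition | yes | not named | yes |
| Disability or incapacity | yes | not named | **no** |
| Hospitalization | **no** (general AE list only) | not named | yes |
| Suicidality | **no** (thoughts or attempts in general AE list only) | yes | **no** |

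Death and life-threatening events are serious in both sections. Hospitalization, suicidality and disability or incapacity are not treated alike: two criteria agree and three disagree.

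Taking the events in turn:

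1. *Suicidal thoughts with no attempt.* Not on the serious list in {17}; a serious AE by the wording of {28a}. If treatment-related, the event is still not on the serious-reaction list in {28a} unless it is life-threatening or needs admission. Section {28a} is therefore not consistent with itself on this item.
2. *Suicide attempt.* It may qualify under {17} as life-threatening, depending on the attempt. Section {28a} does not name attempts, but they fall within the ordinary meaning of suicidality. Completed suicide is a death and is serious in both sections.
3. *Treatment-related hospital admission.* Serious and immediately reportable under {28a}; not on the serious list in {17}.
4. *Admission unrelated to treatment.* Not on the serious list in {17}, and outside the reaction list in {28a}, which covers related events only. The sections do not conflict here.
5. *Treatment-related disability or incapacity.* Serious in {17}; missing from the serious-reaction list in {28a}, and so outside the immediate report.

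The session forms do not settle the matter. The 1-to-3 grade on the ORPHYS form measures severity, which is a different attribute from seriousness.

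**The case against.** Several stronger readings are tempting, and the document does not support them.

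- *Immediate reporting depends on which section is followed.* A reader might infer two competing reporting rules. Only {28a} contains one, and it covers treatment-related events only. Harms {17} deals with recording and publication and does not cancel that rule. The reporting gap is narrower: events called serious elsewhere that the reaction list leaves out.
- *The Harms section classes admissions and suicide attempts as non-serious.* Its general list also contains death, which is on the serious list too. The general list is therefore an umbrella of event types, and being on it does not make an event non-serious. The supportable point is the absence of these items from the serious list.
- *Every admission among the 160 patients is open to two classifications.* Unrelated admissions, likely the larger share in advanced cancer, are on neither serious list.
- *Treatment reactions could not be identified under TAU.* The form description says only what the form includes; Harms {17} states that relatedness is documented after TAU sessions; and the retention section {25b} uses the same occurrence-and-severity shorthand for both arms, although the ORPHYS form does carry a relatedness rating. The short wording does not show that the field is missing.

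It can also be argued that the suicidality wording in {28a} names risks of concern and is not a definition, that suicidality triggers immediate internal notification whatever its label, and that all events will be published, so none is lost. The first argument has some force, since the phrase omits even life-threatening events, but it still labels suicidality a serious AE in a document whose serious list omits it. The second concerns contact with the principal investigator and local study manager, which settles neither classification nor the ethics report. The third is right, and confines the publication effect to the category in which an event is counted.

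A journal article may leave detailed seriousness criteria to the full protocol. That excuses an omission. It does not excuse stating lists that disagree.

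**Conclusion.** The point stands as a contradiction in the stated safety classification. Suicidality events and treatment-related admissions may or may not count as serious in the published results, and a treatment-related disability or suicidality event can be serious under one list yet lie outside the immediate ethics-committee report. Unrelated admissions are not affected, and no event goes unpublished.

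The size in events cannot be given, because the document states no rates for admission, suicidality or disability. The conclusion rests on reading the parenthetical lists as the criteria to be applied. Neither the serious list in {17} nor the serious-reaction list in {28a} is marked as illustrative, whereas {28a} does mark its examples of mild to moderate events that way. It also assumes that no document outside the article ranks one list above the other. Enrollment began in October 2025, so events may already be under classification; whether sites have in fact classified differently is unknown. The primary efficacy analysis is not touched.

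**What to change.** Reconcile Harms {17}, the data monitoring section {28a} and the session forms under Therapy process outcomes into one set of seriousness criteria. State once, for each of death, life-threatening event, hospitalization, suicidal thoughts, suicide attempts and disability or incapacity, whether and when it is serious. Apply that set identically to serious adverse events, serious treatment reactions, the immediate report and the publication, in both arms. Which classification to adopt is for the investigators and the monitoring board; this review takes no position.

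As a minor alignment, make the description of the TAU form match Harms {17}, which already says that relatedness is documented after TAU sessions.

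The cost is protocol wording and a check that the forms carry the agreed fields. Events recorded since enrollment began should be reclassified once under the agreed criteria.

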### Participant timeline {18}

Table 2 shows the schedule of enrollment, intervention, and assessments.

**Table 2 Tab2:**
[figure not shown]
Participant timeline: schedule of enrollment, intervention, and assessments

^a^Assessment is conducted with family caregivers

^b^Arrows indicate continuous delivery of intervention

^c^For a detailed list of assessments see Table S1 in the supporting information

### Sample size {19}

Based on the results for demoralization we found in the pilot study (SD = 5.4), a mean 2-point difference on the Demoralization Scale between ORPHYS and TAU post-intervention is clinically relevant resulting in a medium-sized effect of Cohen’s d = 0.5 [95]. Calculating a two-tailed t-test with a power of 80% (1-β, true positive) and a type I error probability level of alpha = 0.05, 128 patients (64 patients per group) are needed for the post-intervention assessment to detect a moderate effect size of Cohen’s d = 0.5. Assuming a completion rate of 80% (due to patients’ death or physical deterioration) between baseline and post-intervention assessment, 160 patients need to be randomized. Taking into account a participation rate of 70%, 229 patients need to fulfill inclusion criteria.

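### A 2-point difference at the stated SD of 5.4 is d = 0.37, not 0.5, so on the protocol's own t-test 64 per group gives 80% power for 2.7 points and about 55% for 2 points

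*Protocol article*

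**What the plan says.** All the figures stand in the protocol article, section Sample size {19}. The variability comes from the pilot: "Based on the results for demoralization we found in the pilot study (SD = 5.4". The target is a difference in points, and the section presents the standardised effect as following from it and the SD: "a mean 2-point difference on the Demoralization Scale between ORPHYS and TAU post-intervention is clinically relevant resulting in a medium-sized effect" of d = 0.5, with a literature citation attached.

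The calculation then uses the standardised effect alone. The test is given as "Calculating a two-tailed t-test with a power of 80" percent, with "a type I error probability level of alpha = 0.05". The result is "128 patients (64 patients per group) are needed for the post-intervention assessment to detect a moderate effect size" of d = 0.5. This is raised to 160 randomized for 80% completion and to 229 eligible for 70% participation.

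The planned primary analysis is described elsewhere, in Statistical methods {27a}. It is a linear mixed model on change from baseline, with group, time point and their interaction as fixed effects, and a confirmatory group contrast at 6 months. Baseline score is not listed as a covariate. Neither section gives a correlation between baseline and follow-up, or says whether 5.4 is the SD of scores at one time or of change scores.

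**The concern.** Cohen's d is the mean difference divided by the SD. The section gives the difference, the SD and d in one sentence and presents the third as a consequence of the first two, but the division does not give 0.5. The gap between 0.37 and 0.5 is too wide for rounding.

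The 2 points are the only clinical basis offered for the effect size, and the sample size rests on d = 0.5. If the two do not correspond, the stated 80% power does not belong to the difference that the protocol calls clinically relevant. This affects the trial's single confirmatory test, which readers will set against the stated target and power.

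**Working it through.** **Inputs.** From Sample size {19}: SD 5.4, difference 2 points, d = 0.5, two-sided alpha 0.05, power 80%, 64 per group, 80% completion, 70% participation. From Sequence generation {21b}: 1:1 allocation.

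**Step 1: reproduce the stated sample size.** The two-sample t-test (noncentral t) with d = 0.5 needs 63.8, so 64 per group and 128 in total. Then 128/0.80 = 160 and 160/0.70 = 228.6, so 229. Every stated count reproduces from d = 0.5.

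**Step 2: check the step from points to d.**
- 2/5.4 = 0.370
- points that match d = 0.5 at SD 5.4: 0.5 × 5.4 = 2.7
- SD that matches d = 0.5 for 2 points: 2/0.5 = 4.0

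The stated d does not follow from the stated difference and SD.

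**Step 3: power on the stated t-test with 64 per group.** The noncentrality parameter is d × √(n/2), with 126 degrees of freedom.
- d = 0.5 (2.7 points): 0.5 × √32 = 2.83, power 80.1%
- d = 0.370 (2 points): 0.370 × √32 = 2.10, power 54.7% (normal approximation 55.4%)

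If all 160 randomized patients were evaluable (80 per group), power for 2 points would be 64%. For scale, 80% power for 2 points at SD 5.4 needs 115.4, so 116 per group. That is 232 evaluable and 232/0.80 = 290 randomized.

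**Step 4: the planned change-from-baseline analysis.** The 6-month contrast is treated here as a two-sample comparison of change scores with 64 complete patients per group. This leaves out the site and therapist effects and any information from other visits. Assume that 5.4 is a cross-sectional SD, equal at both times. The SD of change is then 5.4 × √(2(1 − r)), where r is the assumed baseline-to-follow-up correlation.

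| r (assumed) | SD of change | d for 2 points | Power, 64 per group |
|---|---|---|---|
| 0.3 | 6.39 | 0.313 | 42% |
| 0.5 | 5.40 | 0.370 | 55% |
| 0.6 | 4.83 | 0.414 | 64% |
| 0.7 | 4.18 | 0.478 | 77% |
| 0.8 | 3.42 | 0.586 | 91% |

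An SD of change of 4.0, and so 80% power, needs r = 1 − (4.0/5.4)²/2 = 0.73. If 5.4 is already the SD of change, the result is that of step 3, about 55%.

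**The case against.** The strongest reply is that the sample size is right for what it says it detects. The counts 64, 128, 160 and 229 all follow from d = 0.5, and the section names d = 0.5 again as the effect to be detected. What fails is the translation from points to d. Because the citation attached to that step cannot be consulted here, one cannot tell whether the 2, the 5.4 or the 0.5 is the mistake. This stands, and it decides the form of the remedy: the figures must be reconciled, and the documents do not show that the trial must be enlarged. It does not remove the contradiction, since the 2 points are the only clinical justification offered for d = 0.5.

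A second reply is that the planned model uses baseline scores and may be more efficient than the t-test. That is possible, but the sample size section does not claim it and gives no correlation to support it. A change score also loses power against a follow-up score when r is below 0.5.

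A third reply is that an SD from a small pilot is imprecise. Section 15a reports 25 included patients. If the SD came from all of them (an assumption), its 95% interval is about 4.2 to 7.5, and t-test power for 2 points runs from about 76% down to 32%. So 54.7% should not be read as exact. An SD of 4.0 still lies outside that interval.

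A reader might infer that the trial as such has 55% power. The documents do not support that: the figure belongs to the unadjusted t-test, and power under the planned model could lie on either side of it. A reader might also infer that a null result will be taken to exclude a relevant benefit; nothing in the protocol commits to that interpretation.

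**Conclusion.** The effect size is wrong as written. A difference of 2 points at SD 5.4 is d = 0.37, and no other figure in the article reconciles it with 0.5. On the protocol's own two-sided t-test, 128 evaluable patients give 80% power for 2.7 points and about 55% for 2 points. That conclusion takes the stated SD at face value and needs no other assumption.

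Power for 2 points under the planned model cannot be fixed from the article. The 42% to 91% range rests on assumed correlations of 0.3 to 0.8 and on 5.4 being a cross-sectional SD, equal at both times. If 5.4 is the SD of change, about 55% applies to the planned analysis too, within the simplification made in step 4. The error is in the stated justification and power; the planned analysis itself is unaffected.

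**What to change.** Correct Sample size {19} so that the difference, the SD and d agree:

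- State that 128 evaluable patients give 80% power for 2.7 points (d = 0.5 at SD 5.4) and about 55% for 2 points (d = 0.37) on the two-sided t-test.
- Say whether 5.4 is a cross-sectional SD or the SD of change.
- If 2 points stays the target, give power for the planned change-score model over a range of correlations informed by the pilot. A single pilot correlation is too imprecise to rely on. Quote baseline-adjusted power only if a baseline covariate is added to the model; otherwise, if 5.4 is cross-sectional, it would flatter the planned analysis (at r = 0.5, 67% against 55%).
- If d = 0.5 is the intended target, state it as 2.7 points and justify the relevance of that difference.

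The cost is wording and a short recalculation. No extra patients are required and no analysis changes. The stated power for 2 points becomes less favourable unless the pilot data support a correlation of about 0.73 or more. Recruitment runs to December 2027 and no interim analysis is planned, so the correction can be made before any comparative result is known.

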### Eligibility criteria for sites and those delivering interventions {14b}

ORPHYS will be provided by licensed psychodynamic psychotherapists or psychodynamic psychotherapists in advanced training. Across study sites, 20 study therapists (physicians, psychologists) received an 8-h ORPHYS training. The training conveys psychodynamic considerations specific to advanced cancer patients (frequent emotional conflicts, destabilization of typical coping patterns, and development of existential symptoms), treatment technique (therapeutic stance promoting positive transference, addressing physical symptoms, transference dynamics and conflicting relational patterns frequently reported for this population) [34], and works with case studies. Study therapists are supervised at a ratio of 1:4 throughout the entire study period.

TAU will be provided by physicians or master-level psychologists with experience in psycho-oncological care. TAU can be provided via the outpatient service of the study center. Patients can also be referred to external care providers in accordance with the routine procedures at the respective study center.

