## Statistical methods

### Statistical methods for primary and secondary outcomes {27a}

To investigate the treatment effect for the primary outcome demoralization at post-intervention, we will calculate a linear mixed model using the difference between post-intervention and baseline scores (change-from-baseline model). The model will include intervention (ORPHYS vs. TAU), time point and the interaction intervention group X time point as fixed effects to test group differences and a random intercept to account for inter-individual differences. The model will include trial site, therapists and patients as nested random effects. We will conduct a confirmatory analysis of the between-group contrast at the 6-month follow-up.

We will investigate treatment effects for the continuous secondary outcomes (death anxiety, dignity-related distress, quality of life) at post-intervention accordingly. To investigate the treatment effect for the binary outcomes (mental disorders) at post-intervention, we will calculate a mixed-effects logistic regression model with intervention (ORPHYS vs. TAU), time point and the interaction intervention group X timepoint as fixed effects as well as trial site, therapists and patients as nested random effects.

Analyses will be performed two-sided with alpha = 0.05. There will be no adjustment for multiple testing. While analysis of the primary outcome will be confirmatory, all other analyses will be exploratory, and specified *p*-values for these analyses should be interpreted descriptively. All analyses will be performed using IBM SPSS Statistics 29 [97] and R, version 4.5.2 [96].

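### The 80% power rests on independent patients and makes no allowance for the therapist clustering in the primary model, so it is unsupported and probably optimistic

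*Protocol article*

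**What the plan says.** The protocol article, Sample size {19}, bases the trial on a comparison of two independent groups: "Calculating a two-tailed t-test with a power of 80" per cent, with a "type I error probability level of alpha = 0.05" and an aim "to detect a moderate effect size of Cohen’s d = 0.5". The result is that "128 patients (64 patients per group) are needed for the post-intervention assessment". The only inflation after that is for an 80% completion rate, which gives 160 randomised. No ICC, design effect or caseload is named.

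Statistical methods {27a} analyses the same outcome with a linear mixed model on change from baseline, with a confirmatory group contrast at 6 months. On clustering it says: "The model will include trial site, therapists and patients as nested random effects". The therapist level is not limited to one arm.

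Eligibility criteria for sites and those delivering interventions {14b} reports that "20 study therapists (physicians, psychologists) received an 8-h ORPHYS training". TAU is given by physicians or psychologists through the centres' outpatient services, and patients may also be sent to external providers. The number of TAU providers is not stated.

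**The concern.** The analysis section allows for patients of the same therapist having correlated outcomes. The sample size section sets that correlation to zero without saying so. Both statements are in the text, so this is a mismatch within the plan and not a detail left to another document.

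At stake is how the result will be read. If the trial finds no difference, readers will judge that finding against a claimed 80% power. If the real figure is nearer 70%, a null result says less than it appears to.

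**Working it through.** **Inputs from the protocol article.** d = 0.5, two-sided alpha 0.05, 64 analysed per arm, 20 ORPHYS therapists, and a raw difference of 2 points with SD 5.4.

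**Assumed inputs (not in the document).** Therapist ICC 0.02, 0.05 or 0.10; 10 or 20 TAU providers; equal caseloads; baseline to 6-month correlation r of 0.4 to 0.6, with equal SDs at the two times.

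**Step 1: reproduce the stated figure.** The noncentrality is 0.5 / √(1/64 + 1/64) = 2.83 on 126 degrees of freedom, giving power 80.1%. With 63 per arm it is 79.5%. Also 128 / 0.80 = 160. The stated numbers are correct for independent patients, and 64 is the smallest group size that reaches 80%.

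**Step 2: caseloads.** ORPHYS: m = 64/20 = 3.2 analysed patients per therapist. TAU: m = 3.2 with 20 providers, 6.4 with 10.

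**Step 3: design effect per arm.** DE = 1 + (m − 1) × ICC. Noncentrality = 0.5 / √(DE₁/64 + DE₂/64), keeping 126 degrees of freedom.

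Example, ICC 0.05 and 10 TAU providers: DE₁ = 1 + 2.2 × 0.05 = 1.11; DE₂ = 1 + 5.4 × 0.05 = 1.27; noncentrality = 0.5 / √(2.38/64) = 2.59; power 73.0%.

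| Clustering assumed | ICC 0.02 | ICC 0.05 | ICC 0.10 |
|---|---|---|---|
| ORPHYS only | 79.3% | 78.0% | 75.9% |
| Both arms, 20 TAU providers | 78.4% | 75.9% | 71.9% |
| Both arms, 10 TAU providers | 77.2% | 73.0% | 66.6% |

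At ICC 0.01 the two lower rows are 79.3% and 78.7%, a loss of one to two points. Uneven ORPHYS caseloads (assumed coefficient of variation 0.6, replacing m by m × 1.36 in DE) change the first row to 78.8 / 76.9 / 73.8%.

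**Step 4: the change-from-baseline outcome.** A change score has SD equal to √(2(1 − r)) times the single-time SD, so d becomes 0.5 / √(2(1 − r)). With the same ICC of 0.05 applied to the change score and 10 TAU providers:

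| r | d on the change score | Power |
|---|---|---|
| 0.4 | 0.456 | 65.1% |
| 0.5 | 0.500 | 73.0% |
| 0.6 | 0.559 | 82.0% |

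With 20 TAU providers, the same ICC gives 68.2% at r = 0.4, 75.9% at 0.5 and 84.6% at 0.6.

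**Step 5: the effect size in the same paragraph.** The article says "a mean 2-point difference on the Demoralization Scale between ORPHYS and TAU post-intervention is clinically relevant" and takes its SD from the "pilot study (SD = 5.4"). That is 2/5.4 = 0.37, not 0.5. With 64 per arm and no clustering, d = 0.37 gives 54.7% power.

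**The case against.** The strongest reply has four parts.

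- **No sum is wrong.** The figures 128 and 160 follow from the stated inputs. This stands. The fault is an omitted variance component, not an arithmetic slip.
- **A journal article may leave the allowance to the full protocol.** This carries limited weight. The article gives the calculation complete (test, alpha, power, effect size, N, completion), and 64 per arm is exactly what independence requires, so no hidden allowance can be inside it.
- **The large losses depend on assumed numbers.** This stands. From the one documented count, 20 ORPHYS therapists, the loss is one to four points. The 67% needs both ICC 0.10 and 10 TAU providers. Referral to external providers could make TAU clusters smaller; the true number could also be below 10.
- **The change-from-baseline model may recover the loss.** It may, if r is clearly above 0.5. It makes matters worse below 0.5, and the article claims no such gain.

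A reader might infer that the design definitely delivers less than 80%, or that TAU providers must be few at each centre. The document supports neither. It gives no ICC, no TAU provider count and no baseline correlation, so the sign of the net departure from 80% under the full planned model is not known.

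**Conclusion.** The point holds in limited form. The stated power omits a source of variance that the plan's own primary model includes, and there is no margin to absorb it. For the t-test contrast as stated, any positive therapist ICC gives less than 80%: about 76 to 79% if only ORPHYS is clustered, and 67 to 78% if both arms are, over ICCs of 0.02 to 0.10 and 10 to 20 TAU providers. These figures assume equal caseloads and 126 degrees of freedom.

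For the planned change-score analysis, the 80% is unsupported and probably optimistic unless the ICC is near zero or the baseline to 6-month correlation is clearly above 0.5.

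The effect-size mismatch is a separate and larger problem: about 25 points, against two to seven for clustering at ICC 0.05. Correcting either one leaves the other in place.

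**What to change.** Keep 160 randomised. Rewrite the power paragraph so that it:

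- states power for 128 analysed patients, for the 6-month contrast, under the planned mixed model;
- gives the assumed therapist ICC, the caseload per arm including the number of TAU providers, and the assumed baseline to 6-month correlation, each with its source;
- reports a range across those assumptions in place of a flat 80%;
- reconciles the 2-point difference, the SD of 5.4 and d = 0.5 in the same revision.

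The last item must not be done separately. A range of 67 to 79% printed around d = 0.5 alone would rest on an effect size that the paragraph's own figures do not give.

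The cost is one rewritten paragraph and a less favourable power statement. It needs no extra patients and no change to the analysis model.
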